#### **8.2.2 Control Intervention**

The control intervention will be a minimal intervention - *Brief advice (BA)* - delivered in approximately 5 to 10 minutes while in the ER by the same qualified research clinicians (psychologist, clinical social worker, or nurse). It will consist of a standardized computer-based brief structured feedback and advice to cut down drinking, with referral to specialist services for the more severe patients (based on the Alcohol Use Disorders Identification Test score included in the baseline assessment).

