### **11.4 Planned Analyses**

#### **11.4.1 Datasets to be analysed, analysis populations**

Primary analyses of the efficacy of the intervention (randomized controlled trial) will use all data available from all participants included in the trial. Analysis will be performed in an intention to treat paradigm (i.e. participants having left the ER without finishing the intervention, and/or not receiving intervention booster sessions will be analyzed in the intervention group).

Secondary analysis of mechanisms (Aim 3 of the project) will use data available for the corresponding analyses (e.g. participants with audio-recorded sessions for psycholinguistic coding; randomly selected sub-sample for qualitative analyses). Also, moderation analyses are designed as part of the mechanism analyses. For these, the relative efficacy of the BMI will be tested as an interaction with participants' characteristics, such as age, gender, alcohol problems severity, readiness to change, or personality traits.

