#### 11.4.3 Secondary Analyses

Analyses of intervention mechanisms (Aim 3 of the project) will include the following analyses:

*Moderation.* Separate GEE models will test the main effect of treatment on outcome, followed by the effect of each moderator variable, and then the interaction of the treatment with each moderator variable.

*Mediation.* To examine mediators of the main effect of the MI intervention on outcomes, we will use Model 4 of the PROCESS algorithm developed by Hayes (2013). Here, regression analyses are used to test path *a* (the effect of the treatment condition on the hypothesized mediators) and path *b* (the effect of each respective mediator on outcomes, while also controlling for the treatment effect on outcomes). Then indirect effects are estimated using bootstrapping, a nonparametric resampling procedure that does not impose the assumption of normality of the sampling distribution (Hayes, 2013; Preacher & Hayes, 2008).

*Moderated mediation* aims at measuring if the effect is transmitted through the designated mediators only under specific circumstances. Several models of the PROCESS algorithm (e.g. 7, 9, 58) allow calculation of moderated mediation (also known as conditional indirect effects) (Hayes, 2013) (Hayes, 2013). These different models specify which path (*a*, *b*, both) of the mediated relationship are moderated. As in mediation, bootstrapping is used to derive conditional indirect effects.

*Qualitative analyses.* In addition to the quantitative analysis of interventions' mechanisms exposed above, we will use qualitative techniques to analyze intervention and follow-ups feedback. A random sub-sample of 20 BA and 20 MI sessions will be transcribed and analyzed using thematic analysis and recursive abstraction techniques (Maxwell, 2005). In addition, semi-structured interviews will be conducted after the 1-month and 12-month follow-up questionnaire with another randomly selected 10 patients having received BA and 10 MI sessions. Topics addressed will be qualitative assessment of potential short-/long-term changes experienced during the follow-up period and their relation or not with the intervention received.

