Regarding hypotheses, the proposed research will be one of the first prospective study designed to evaluate the mechanisms of alcohol BMI outcomes, which is in line with recently recommended priorities in clinical trial design (Longabaugh and Magill, 2011). Specifically, we will analyze treatment effects within a larger conceptual framework of mechanisms of behavior change (see Figure below). The mechanisms investigated here are all indicated as promising candidate variables in the seminal monograph on factors impacting addiction treatment effects recently published by Miller and Moyers (2015). In this model, the main effect (red arrow) between treatment and change in alcohol use (distal outcome) is explained (or mediated) by therapists' and patients' within-session behaviors (e.g. MI skills and change language), by the patients' experience of the treatment, and by patient proximal cognitive or behavioral changes (e.g. increased self-efficacy, readiness to change, Longabaugh *et al.*, 2005; Moos, 2007). Patient behaviors during treatment might influence their experience of the treatment and thus their outcome, but also influence therapist behaviors (as indicated by bidirectional arrow; e.g. Moyers and Martin, 2006; Gaume *et al.*, 2010). Finally, what happens during the session (therapist and patient behaviors) may be influenced by several moderating factors (e.g. Karno and Longabaugh, 2007; Gaume *et al.*, 2009; Gaume *et al.*, 2016).

These factors mainly are the therapist and patient characteristics, such as age, gender, therapist clinical experience, patient alcohol problems severity, readiness to change, or personality. (Note: our design will not permit tests of therapist characteristics which will be underpowered).

[figure not shown]

Quantitative analyses will be performed by the study PI ([name]), in collaboration with research collaborator [name], and consulting from study co-Is ([name], [name], [name]) and international collaborators ([name], [name]).

Qualitative Analyses will be performed by research collaborator [name] and [name], with consulting from study PI ([name]), co-Is ([name], [name], [name]), and international collaborators ([name], [name]).

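### The mediation analysis assumes one mediator-outcome slope for both arms and plans no check of it, although some mediators arise in sessions that differ in kind

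*Protocol*

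**What the plan says.** Section 11.4.3 of the protocol states the mediation model without alternative: "we will use Model 4 of the PROCESS algorithm". Path a is "the effect of the treatment condition on the hypothesized mediators", and path b is "the effect of each respective mediator on outcomes, while also controlling for the treatment effect on outcomes". Indirect effects are bootstrapped. No treatment-by-mediator term appears.

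The hypotheses later in 11.4.3 name three classes of mediator: therapist and patient "within-session behaviors (e.g. MI skills and change language"), the patient's experience of the treatment, and proximal changes such as self-efficacy and readiness to change. Under the Phase 3 rows of section 9.1, every recorded session with consent is coded, whichever arm it belongs to.

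The sessions differ. BMI lasts 20 to 60 minutes, with telephone boosters if the participant agrees (8.2.1). Brief advice takes about 5 to 10 minutes: "It will consist of a standardized computer-based brief structured feedback and advice to cut down drinking" (8.2.2).

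On moderated mediation, 11.4.3 says: "Several models of the PROCESS algorithm (e.g. 7, 9, 58) allow calculation of moderated mediation". Section 11.4.1 describes moderation as the relative efficacy of BMI "tested as an interaction with participants' characteristics". Study arm is nowhere named as a moderator of path b.

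**The concern.** A single path-b slope is right when a unit of the mediator predicts the outcome equally in both arms. For proximal changes measured on the same scales in everyone, that is a reasonable default. For MI skills, change language or the experience of the session, the protocol gives no reason why the relation should be the same in a motivational interview and in a short scripted feedback, and it plans no test.

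Aim 3 asks how the intervention works, and Aim 4 (section 3.1.5) finalises the BMI model partly on the answer. If the slopes differ, a component of BMI could be retained or dropped on a slope taken partly from brief-advice sessions. This can happen with a single mediator and no confounding of path b.

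**Working it through.** **Inputs.** The protocol gives no effect size, SD or power for any mediator, so there is no figure of its own to reproduce on this point. From section 11.2: 172 per arm, 1:1 allocation, attrition of 5 to 20%. At 20% attrition, 172 × 0.80 = 137.6, taken as 138 per arm. The rest is assumed: treatment shifts the mediator by a = 0.8; mediator SD is 1 in BMI and 1 or 0.5 in brief advice; residual outcome SD is 1; tests are two-sided at 5%.

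**What Model 4 estimates.** With treatment as a covariate and equal arms, the common slope is

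b = (v₁b₁ + v₀b₀) / (v₁ + v₀),

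where b₁, b₀ are the BMI and brief-advice slopes and v₁, v₀ the mediator variances. The weights are 0.5 and 0.5 with equal SDs, and 1/1.25 = 0.8 and 0.25/1.25 = 0.2 with half the SD in brief advice.

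**Precision.**
- Common slope: 1/√(138 × 2) = 0.060 with equal SDs; 1/√(138 × 1.25) = 0.076 with half the SD.
- BMI slope alone: 1/√138 = 0.085, which is 1.41 or 1.12 times as large.
- Path a: 0.8/√(2/138) = 6.6 standard errors, so the verdict on a × b follows path b.

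**Results.** The hand value is Φ(|b|/SE − 1.96), plus the small opposite tail where it matters. The simulated value is the share of trials whose 95% interval for a × b excludes zero. Each cell gives Model 4 against the BMI slope.

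| Slopes (BMI, advice) | Advice SD | Model 4 slope | Indirect effect | By hand | Simulated |
|---|---|---|---|---|---|
| 0, −0.3 | 1 | −0.15 | −0.12 v 0 | 70% v 5% | 67% v 6% |
| 0, −0.3 | 0.5 | −0.06 | −0.048 v 0 | 12% v 5% | 12% v 4% |
| −0.3, 0 | 1 | −0.15 | −0.12 v −0.24 | 70% v 94% | 71% v 94% |
| −0.3, 0 | 0.5 | −0.24 | −0.192 v −0.24 | 88% v 94% | 87% v 93% |
| −0.3, +0.3 | 1 | 0 | 0 v −0.24 | 5% v 94% | 5% v 92% |
| −0.2, −0.2 | 1 | −0.20 | −0.16 v −0.16 | 91% v 65% | 91% v 63% |
| −0.15, −0.15 | 1 | −0.15 | −0.12 v −0.12 | 70% v 42% | 69% v 39% |

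Simulated values move by a few points between runs.

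**Smaller path a.** These runs used the percentile bootstrap and equal SDs, at 172 per arm (138 in brackets).
- a = 0.5, slope 0 in BMI and 0.3 in brief advice: declared in 77% (67%) with Model 4, against 4% (7%) with the BMI slope.
- a = 0.5, slope 0.3 in BMI and 0 in brief advice: detected in 78% (64%) against 96% (90%).
- a = 0.25: the first comparison becomes 47% (38%) against 3% (3%), and the second 49% (32%) against 66% (48%).

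**The case against.** **Brief advice may vary little.** A standardised script should compress variation in MI skills and change language, and the common slope then leans towards BMI. This stands: at half the SD the excess falls to 12% against 4%, and the power loss to 87% against 93%. A reader might infer that Model 4 would hide a real mechanism altogether. That needs slopes of opposite sign, equal size and equal SDs. With half the SD in brief advice, the opposite-sign case is still detected in about 66% of trials (slope 0.8 × −0.3 + 0.2 × 0.3 = −0.18). Nothing in the protocol suggests opposite signs.

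**Equal slopes may be a fair default.** This stands for readiness and self-efficacy, which are measured identically in both arms. A reader might infer that equal slopes are the least likely case. The protocol shows only that the assumption is unsupported for the within-session mediators, not that it is false.

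**Arm-specific estimates cost power.** This also stands. With equal slopes of −0.2, power is 63% against 91%. With slopes of −0.2 and −0.1, Model 4 still does slightly better (71% against 66%). A reader might infer that Model 4 should be demoted and every mechanism claim made to rest on the BMI slope. That rule would miss many true mediators.

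**Two indirect effects exist.** When treatment and mediator interact, the effects at the BMI slope and at the brief-advice slope are both legitimate mediation effects. Model 4's rejection in the first table row is therefore an error only as a statement about how BMI works, which is nevertheless Aim 3's question.

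**Moderated mediation may cover it.** The list of models is open, and moderation of path b is allowed. But the moderators described are mainly patient and therapist characteristics, and 11.4.1 concerns efficacy, not indirect effects. No arm-specific slope enters any planned indirect effect.

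**A statistical analysis plan may supply the check.** None is shown. If it contains one, the point is met. The protocol itself fixes the model and its path b, so this is a choice made and not only a detail deferred.

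**Conclusion.** The concern holds in a limited form. Section 11.4.3 commits to one slope for both arms and plans no check of it, although some mediators come from sessions that differ in kind. If the slopes differ, the Model 4 indirect effect is a variance-weighted average of two arm-specific effects and may describe neither arm.

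The damage ranges from small to large according to how much the mediator varies under brief advice. For a mediator inert in BMI, declaration runs from about 12% to 67%, against 4 to 6% with the BMI slope. For one active only in BMI, power is 87% down to 71%, against 93 to 94%. All of this rests on assumed values of a, the slopes and the SDs. If the slopes are equal, Model 4 is unbiased and more powerful.

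A reader might infer that the trial's efficacy conclusion or sample size is in doubt. Neither is touched: the primary GEE comparison and N = 344 do not use the mediation model. Aim 4 also draws on qualitative work, so it does not hang on Model 4 alone.

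**What to change.** Keep Model 4 and add to section 11.4.3, for each mediator, a second path-b model containing the treatment × mediator product. Report three things beside the Model 4 figure:

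- the interaction estimate with its interval;
- the indirect effect at the BMI slope, with a bootstrap interval;
- the indirect effect at the brief-advice slope, with a bootstrap interval.

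State that where the slopes differ materially, conclusions about how BMI works rest on the BMI-slope effect. State also that a non-significant BMI-slope effect does not by itself rule a mediator out.

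The cost is one extra model per mediator and a few sentences; no new data are needed. The arm-specific estimates are less precise, with a standard error about 1.1 to 1.4 times the pooled one. Fewer than 138 per arm may be available for mediators that need a recorded session with consent.

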#### 11.4.4 Interim analyses

There will be no interim analyses.

#### 11.4.5 Safety analysis

Not applicable (see Chapter 10. Safety).

#### 11.4.6 Deviation(s) from the original statistical plan

Any deviation(s) from the original statistical plan will be described and justified in the final report.

### 11.5 Handling of missing data and drop-outs

Preliminary analyses will examine variable distributional properties, correlations, and patterns of missing data to inform data-analytic procedures. In the event that we identify systematic mechanisms of missingness, we will explore varying techniques to impute missing data (Little and Rubin, 2002); primary analyses will use all available data in an intent-to-treat paradigm.

## **12. QUALITY ASSURANCE AND CONTROL**

### **12.1 Data handling and record keeping / archiving**

#### **12.1.1 Case Report Forms**

All trial data (demographic informations, questionnaires, randomization, ...) of each participant will be directly recorded in an electronic case report form (eCRF, secuTrial software) independently managed by the Clinical Trial Unit, Lausanne, warranting data integrity, security, quality and traceability. Only authorized person (delegated by the principal investigator) will be allowed to proceed to eCRF entries.

The only exception is the patient rating of the treatment questionnaire which is a 12-item questionnaire assessing participant's rating of the intervention right after the intervention. This questionnaire will be self-reported using a paper/pencil questionnaire to be placed in a sealed envelope by the participant and later entered by research assistant to avoid that research clinicians have access to participant's rating of the session.

#### **12.1.2 Specification of source documents**

Signed informed consent forms, Contact information forms, and Patient rating of the treatment questionnaires are considered paper source documents and will be stored in the investigator site file in locked cabinets at the Alcohol treatment center, Lausanne university hospital.

Socio-demographic data and baseline/follow-up dates will also be considered source documents and will be directly collected in the e-CRF.

#### **12.1.3 Record keeping / archiving**

Paper data and audio-recording will be brought back to the Alcohol Treatment Center by the research clinicians at the end of the inclusion period and immediately secured in file locked cabinets (paper data) or electronically stored on secured servers (audio-recordings).

All paper study data filed in the investigator site file/ trial master file (ISF/TMF) will be archived for a minimum of 10 years after study termination or premature termination of the clinical trial in locked cabinets at the Alcohol treatment center, Lausanne university hospital.

Audio-recordings will be stored using only the participant's identification code. Audio-recordings will be electronically stored on secured servers protected by a password accessible only to psycholinguistic coding staff, clinical supervisors, and qualitative research analysts.

Electronic archives will be stored on secured servers for a minimum of 10 years also.

## **12.2 Data management**

### **12.2.1 Data Management System**

All questionnaires and randomization will be conducted and recorded directly on a secured electronic case report form (eCRF, secuTrial software) independently managed by the Clinical Trial Unit, Lausanne, warranting data integrity, security, quality and traceability.

### **12.2.2 Data security, access and back-up**

Data will be entered directly in the eCRF by research clinicians (baseline procedures, intervention) and research assistants (follow-up questionnaires).

Access to raw data will be granted to the study PI or to research collaborators explicitly allowed to access data by the study PI.

Access to contact data will be granted to the research collaborator in charge of compiling lists for follow-up contacts ([name]). These lists will be given to research assistants in charge of follow-up questionnaires.

Access to all other data will be granted to the study PI or to research collaborators explicitly allowed

to access data by the study PI, e.g. to extract data for analysis.

No one will be permitted to alter data, except a) respective research clinicians/assistants having noticed an error in their own data entry, or b) the study PI or a research collaborator explicitly allowed to by the study PI in case an error has been noted during monitoring or electronic validation. All data alteration will be traced in the software (secuTrial) and will require a justification documented in a comment field. When complete, each eCRF will be validated by the study PI using dedicated entry fields (i.e. a check box "I hereby confirm that data entered are correct and complete", and entry fields for name and date). The built-in traceability of the eCRF software (secuTrial) will guarantee that this signature is valid (PI login/password, date and time of entry).

Backup of electronic data are built-in in the eCRF software (secuTrial) and on CHUV servers.

### **12.2.3 Analysis and archiving**

Data will be extracted for analysis by the study PI or a research collaborator explicitly allowed to access data by the study PI. Data will be extracted to one or several databases compiled on statistical packages (e.g. Stata, SPSS, SAS, R).

Databases will be stored on electronic folders secured on the CHUV servers and protected by passwords. Access to the datasets will be granted to research collaborator explicitly allowed to access data by the study PI.

Databases used for primary analyses as well as secondary analyses later published will be stored on electronic folders secured on the CHUV servers and protected by passwords for 10 years. Databases used for temporary analyses or secondary analyses not retained will be destroyed.

### **12.2.4 Electronic and central data validation**

Data validity, coherence, and completeness will be assessed at several steps. First, control rules will be implemented in the data entry software (secuTrial). Second, coherence of study plan and data collection will be regularly assessed by the study PI throughout the study and discussed during weekly supervision of research staff. Then, monitoring performed by the Clinical Trial Unit, Lausanne (see below) will encompass monitoring of data coherence and completeness, as well as systematic documentation of alteration in the data. Finally, coherence and completeness will be checked when the data will be exported to statistical packages for analyses.

## **12.3 Monitoring**

Monitoring will be performed according to ICH Good Clinical Practice (GCP) by the Clinical Trial Unit, Lausanne. Following a Monitoring Plan and written SOPs, the monitors will verify that the clinical trial is conducted and data are generated, documented and reported in compliance with the protocol, GCP and the applicable regulatory requirements. The principal investigator will provide direct access to all trial related source data/documents and reports for the purpose of monitoring and will answer monitors' questions during monitoring visits.

## **12.4 Audits and Inspections**

No trial audit is planned. However in case of audit and/or inspection by the responsible ethics committee, the study documentation and source data/documents will be accessible to auditors/inspectors and questions will be answered during audits/inspections. All involved parties will keep the participant data strictly confidential.

## **12.5 Confidentiality, Data Protection**

Data protection and confidentiality will be guaranteed. Direct access to source documents will be permitted for purposes of monitoring (12.3), audits and inspections (12.4).

No printed nor online reports will be published with participants' name or possible identification. Audio-recordings will in principle not be used in public, but in case it would, only excerpts not divulging participants identity would be used and voice would be distorted.

Deidentified datasets, protocol, and statistical code will be available for co-investigators, international collaborators, and close collaborators or students to run potential additional secondary analyses. This material might also be made available for consultation during peer-review processes for study publication.

## **12.6 Storage of biological material and related health data**

Coded head hair samples will be stored in locked cabinets at the Alcohol Treatment Center, Lausanne University Hospital, until completion of data collection. Samples will then be transferred to the Forensic Toxicology and Chemistry Unit at the Lausanne and Geneva Universities Centre of Legal Medicine where analyses will be processed.

Samples will be destroyed at the end of the study.

### **13. PUBLICATION AND DISSEMINATION POLICY**

Our findings will be presented during scientific conferences at all phases (intervention development, efficacy study, mechanisms analyses, and model finalization). Several articles will be published in leading peer-review journals in the respective fields: 1 or 2 on intervention development, 1 reporting the results of the RCT, 1 technical paper on EtG concentration in head hair, 2 or 3 on mechanisms analyses, 1 on qualitative analyses of intervention and follow-up semi-structured interviews, and 1 on model finalization.

Anonymized data will be available for co-investigators, international collaborators, and close collaborators or students to run potential additional secondary analysis.

A press conference and press release will be carried out at the end of the project to present the research process and findings to the lay public.

The study PI will coordinate analyses, scientific presentations in conference, and journal articles. Authorship will follow standard guidelines (e.g. International Committee of Medical Journal Editors recommendations).

